### Study design

The study is designed in accordance with the guidelines listed above to answer the question: is it feasible to deliver the Bridges self-management intervention in a group setting? As recommended by guidelines, the study will use a mixed method approach [23]. A randomised waitlist control design will be used and stroke participants will be recruited to the intervention (see Table 1) at different time points. This design will allow comparison between the intervention and waitlist groups (between subjects) and pre-post intervention measures (within subjects). The former will allow sample size calculations to be made. Outcome measures (described in more detail below) collected post intervention also allow any long-term effects of the intervention to be assessed. Once the intervention has been delivered, interviews will be conducted with a sample of the research participants and focus groups will be held with family and friends. Any changes to the protocol are to be discussed with the funders, ethics committee and management panel. A SPIRIT diagram illustrating the course of the study is shown in Table 1.

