### Intervention group

Individuals randomised to the intervention group by a statistician will complete the intervention as soon as they are enrolled. The intervention consists of four consecutive sessions over 4 weeks. They will complete baseline measures before the intervention starts and prior to randomisation. Demographic information will be gathered at baseline for all participants which included age, gender, date of stroke, co-morbidity, aphasia, living situation, ethnicity and employment status. Once they finish the intervention, they will complete outcome measures at three time points: at the end of intervention and then at 2 weeks and 6 months post intervention. Participants may withdraw from the intervention group at any time if they request to do so.

The intervention is a group self-management intervention for stroke which was adapted from the existing one-to-one Bridges self-management intervention. It was designed over a 12-month period (February 2015–February 2016). Five sources were consulted to facilitate the adaption process as follows:MRC guidelines for complex interventions [23]A systematic review of current group self-management interventions (currently unpublished) explored the key features and role of peer support which in turn informed content and structureThe existing Bridges self-management intervention [15] provided core principles and insight to potential challenges that may present during the delivery of the intervention. Also, a Bridges workbook was given to all participants (see Table 1).Interviews with stroke survivors about group self-management interventions [27] provided insights including the need for a group intervention to remain tailored, be in an accessible venue and suggested the addition of a stroke survivor joint-facilitatorA focus group with stroke survivors exploring desirable content. The focus group was made up of seven stroke survivors and one young carer and was facilitated by FJ, the founder of Bridges. Insights such as how to present the group and the need for a separate time for socialising were given.

The resulting group self-management intervention is described in Table 2 using headings suggested by guidelines [22].

**Table 2 Tab2:** Intervention reporting in line with the Template for Intervention Description and Replication (TiDieR) guidelines

Name	Group self-management intervention for stroke
Why (rationale)	Described above in the ‘Background’ section.

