#### Group size

There is differing literature on suggested group size. The Chronic Disease Self-Management Program (CDSMP) has 10 to 15 [28] participants in each group whereas psycho education groups suggesting five to ten [29]. For this group self-management intervention, the group size will be conservative, five to eight stroke survivors. This accounts for the complex nature of stroke. For example, those with aphasia may require the use of additional communication techniques. Family and friends are welcome to attend the sessions.

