### Waitlist group

The waitlist control group will not receive any interaction with the research team during the 6-month wait period. Participants in this condition will complete baseline measures at the start and the end of the waitlist period before randomisation as well as completing questions about demographics as specified above. They will continue to engage with usual care as they would if not taking part in research. Once the wait period is completed, they will take part in the intervention. Outcome measures for this group will be completed at the end of the intervention and again at 2 weeks post intervention. For both the intervention and the waitlist group, questions 2 (what will the level of adherence and attendance to the group self-management intervention be?) and 3 (what will follow-up response rates to questionnaires be?) will be answered using documentation of attendance to the intervention and the return rate of follow-up questionnaires. Participants may withdraw from the waitlist group at any time if they request to do so.

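### The arms share no post-baseline assessment while the waitlist is still untreated, and the between-arm ANCOVA does not say which scores it compares

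*Protocol article*

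**What the plan says.** All references are to the protocol article, Methods.

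- **Intervention group.** Participants "will complete the intervention as soon as they are enrolled". On length: "The intervention consists of four consecutive sessions over 4 weeks". On baseline: "They will complete baseline measures before the intervention starts and prior to randomisation". On follow-up: "they will complete outcome measures at three time points: at the end of intervention and then at 2 weeks and 6 months post intervention".
- **Waitlist group.** "The waitlist control group will not receive any interaction with the research team during the 6-month wait period". On the untreated measures: "Participants in this condition will complete baseline measures at the start and the end of the waitlist period before randomisation". After the wait this arm receives the intervention and is measured at its end and 2 weeks later.
- **Study design.** "This design will allow comparison between the intervention and waitlist groups (between subjects) and pre-post intervention measures (within subjects"). The next sentence says that the first of these, the between-subjects comparison, will make sample size calculations possible.
- **Analysis, Question 7.** An ANCOVA covers both the pre-post and the intervention-versus-waitlist comparison. It names no time point for either. The results are described as preliminary.
- **Group size.** "the group size will be conservative, five to eight stroke survivors".

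**The concern.** A waitlist design earns its between-arm comparison by measuring the control arm, still untreated, at the same time from randomisation as the treated arm. Here each arm's follow-up is set by its own events: the end of the course in one arm and the end of the wait in the other. If no time is shared while the waitlist is untreated, length of follow-up is fixed by arm within any chosen pair of scores. It is then completely confounded with treatment. Baseline covariates such as time since stroke cannot remove this, because the difference arises after baseline.

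At stake is the between-arm part of the answer to Question 7, on the magnitude of change. Any recovery, decline or adaptation between the two measurement times would be counted as intervention effect or would hide it.

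**Working it through.** **Inputs.** From the article: a course of 4 weeks; intervention-arm scores at the end of the course, 2 weeks later and 6 months later; a wait of 6 months without contact; waitlist scores at the end of the wait, the end of its own course and 2 weeks after that. Assumptions: 6 months is M = 26 weeks (24 also tried), the wait starts at randomisation, and the waitlist's course follows directly. L is a possible delay in the intervention arm's start while a group fills; the article gives no figure for it.

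The article gives no figure for this point to reproduce. Its sample size, 50 + 10 = 60, is not affected.

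**Timeline in weeks from randomisation.** The intervention arm is measured at 4 + L, 6 + L and 4 + L + M. The waitlist is measured at M (untreated), then M + 4 and M + 6 (treated).

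| Case | Intervention arm | Waitlist, untreated | Gaps in weeks |
|---|---|---|---|
| M = 26, L = 0 | 4, 6, 30 | 26 | 22, 20, 4 |
| M = 24, L = 0 | 4, 6, 28 | 24 | 20, 18, 4 |
| M = 26, L = 8 | 12, 14, 38 | 26 | 14, 12, 12 |

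The first two gaps are intervention score before waitlist score; the third is the reverse. No case tried, with L from 0 to 8 weeks, gives a shared time with the waitlist untreated. With L = 0 both arms are measured at 4 + 26 = 26 + 4 = week 30, but both have had the intervention by then.

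**Size of the bias.** Assume a true effect of 0.40 SD at every time and untreated change that is linear in both arms, totalling d over 26 weeks. A pair with the intervention score at week t and the waitlist score at week 26 then estimates

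0.40 + d × (t − 26)/26.

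| Intervention score | (t − 26)/26 | d = +0.2 | d = +0.3 | d = −0.3 |
|---|---|---|---|---|
| Week 4 | −22/26 = −0.846 | 0.23 | 0.15 | 0.65 |
| Week 6 | −20/26 = −0.769 | 0.25 | 0.17 | 0.63 |
| Week 30 | +4/26 = +0.154 | 0.43 | 0.45 | 0.35 |

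With an 8-week delay and d = +0.3, the bias is −14/26 × 0.3 = −0.16 for the first score, −12/26 × 0.3 = −0.14 for the second and +12/26 × 0.3 = +0.14 for the late one.

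For scale, with 25 per arm and a baseline correlation of 0.7 (an assumption), the standard error of the ANCOVA difference is about √(2/25 × (1 − 0.7²)) = √(0.08 × 0.51) = 0.20 SD. A bias of 0.25 SD exceeds one standard error; 0.05 SD is about a quarter of one.

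**Wording of the waitlist section.** It places the measures at the end of the wait ahead of randomisation. A wait that results from allocation cannot end before allocation. Read literally, the waitlist would have no untreated score after randomisation at all. The timeline above takes the sensible reading, that only the first set precedes randomisation.

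**The case against.** Several points for the plan stand.

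- **The arms do coincide once.** A reader might infer that they are never measured at the same time after randomisation. The schedule does not support that: both have an assessment at about week 30. It is only a treated-versus-untreated contrast that has no common time.
- **The article does not choose the bad pair.** A reader might take the ANCOVA to compare the week-4 score with the week-26 score. No pair is named. The 6-month wait and the 6-month follow-up form an obvious near match, with little bias on the stated schedule.
- **Waiting for a group to fill does not worsen everything.** Groups of five to eight sit badly with an immediate start, and a reader might conclude that every gap widens. A delay moves the early scores closer to week 26 and widens only the late gap.
- **The drift is assumed.** The documents give no rate of change. Participants have left community rehabilitation, and some had their stroke up to 2 years earlier, so rapid recovery is not the obvious case.
- **Little depends on the contrast.** A reader might infer that the future sample size would be wrong. Study design does link the between-arm comparison to that calculation, but Question 7 and the Discussion draw on the spread of the measures and on dropout, and a shift in means leaves the SD unchanged in this model. The progression considerations (acceptability, serious adverse events, suitability of measures, adherence above 85%) do not use the between-arm difference.

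The choice of pair can ordinarily be left to an analysis plan, and the schedule diagram (Table 1) is not shown. That does not answer the core point. The text itself states the visit times and rules out contact during the wait, so no choice of pair gives equal follow-up.

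**Conclusion.** The concern holds as a fault in the stated assessment schedule, of moderate severity. No post-baseline assessment is shared while the waitlist is untreated. The available contrasts differ in follow-up by about 20 to 22 weeks for the early intervention scores and about 4 weeks for the late one, more for the late one if filling a group delays the start. The possible bias is material for the early pairs (about 0.23 to 0.25 SD for drift of 0.3 SD in either direction) and small for the late pair (about 0.05 SD without delay). These sizes rest on assumed linear drift and a constant effect; the gaps in weeks rest only on the stated schedule and a start without delay. Severity stops at moderate because the study is a feasibility study with no primary outcome and results labelled preliminary.

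**What to change.** 1. Name the between-arm comparison for Question 7: the intervention arm's long-term score against the waitlist's end-of-wait score. Collect both at the same interval from randomisation, in the same window, and before the waitlist starts the intervention.
2. Report the end-of-intervention and 2-week scores as within-arm change only.
3. Correct the Waitlist group sentence so that only the first set of measures precedes randomisation.
4. Optional, if a short-term contrast is wanted: one waitlist questionnaire at the matching early time.

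Items 1 to 3 cost protocol wording and a changed questionnaire date for participants not yet at follow-up. Enrolment began in February 2016, so for anyone already measured the actual interval from randomisation should be reported. With the clock set at randomisation, time since the end of the course will vary with any group-fill delay, so that delay should be recorded. Item 4 costs one contact in a wait meant to be contact-free, plus help by phone or in person for those who need it. Baseline should not be repeated after allocation in one arm to deal with the delay, since that would make the ANCOVA covariate differ in kind between arms.

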#### Group size

There is differing literature on suggested group size. The Chronic Disease Self-Management Program (CDSMP) has 10 to 15 [28] participants in each group whereas psycho education groups suggesting five to ten [29]. For this group self-management intervention, the group size will be conservative, five to eight stroke survivors. This accounts for the complex nature of stroke. For example, those with aphasia may require the use of additional communication techniques. Family and friends are welcome to attend the sessions.

#### Core concepts of the intervention

Social Cognition Theory (SCT) describes the mechanisms which may impact the likelihood of an individual engaging in new behaviours and suggest one of these is social support [30]. SCT suggests that social support along with knowledge and barriers feed directly into an individual’s self-efficacy (an individual’s belief in their own ability to complete a specific behaviour), which in turn contributes to goal setting and ultimately behaviour. This forms an iterative loop with behavioural outcomes feeding back into an individual’s self-efficacy. Consequently, self-efficacy is the central concept of self-management interventions and accordingly self-management interventions showing the most promise are based on self-efficacy [14].

Nine strategies used within Bridges will be translated into a group setting: reflection, knowledge, decision making, problem solving, goal setting, taking action, using resources, collaboration and self-discovery. As with the components of SCT, the Bridges strategies link together and can be iterative in nature. For example, an individual’s goal may be to walk more (setting goals) as they do so less than they used to (reflection), someone else may suggest walking a dog may make the task more enjoyable and recommend a charity that needs dog walkers (collaboration, knowledge, problem solving, using resources). The individual may then decide to go to the charity to sort this out (taking action, decision making). The outcome of this will then inform future decisions (reflection, mastery, taking action, goal setting).

#### Adverse events

There have been no adverse events reported from previous research on the Bridges one-to-one intervention or other stroke-specific group self-management interventions reported in the literature; hence, this study is considered minimal risk. However, the population we are studying has a natural disease progression, and severe events such as a death may occur. In addition, the research is at the feasibility stage so unexpected risks may occur. As a result, any adverse events will be documented and the ethics committee notified. If any patients present with clinically relevant scores, for example if the Hospital Anxiety and Depression Scale shows severe anxiety and/or depression, we will notify their GP (with their consent).

### Waitlist group

The waitlist control group will not receive any interaction with the research team during the 6-month wait period. Participants in this condition will complete baseline measures at the start and the end of the waitlist period before randomisation as well as completing questions about demographics as specified above. They will continue to engage with usual care as they would if not taking part in research. Once the wait period is completed, they will take part in the intervention. Outcome measures for this group will be completed at the end of the intervention and again at 2 weeks post intervention. For both the intervention and the waitlist group, questions 2 (what will the level of adherence and attendance to the group self-management intervention be?) and 3 (what will follow-up response rates to questionnaires be?) will be answered using documentation of attendance to the intervention and the return rate of follow-up questionnaires. Participants may withdraw from the waitlist group at any time if they request to do so.

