Once completed, this research will determine if the intervention should progress to a full RCT. It will do so by exploring the acceptability of the intervention, the occurrence of serious adverse events occur, the appropriateness of research measures and adherence rates which should be over 85%. It will also inform the design of future work assessing the efficacy of a group self-management intervention. It will do so in a number of ways. Firstly, this research will help determine the project timeline as information about the number and rate of eligible participants that can be recruited as well as the follow-up questionnaire return rate will be available. Secondly, it will determine whether future work should randomise participants to a condition as their willingness to do so will be documented. Thirdly, the design of the group self-management intervention may be adapted based on the acceptability to stroke survivors and family/friends/carers. Finally, the information to conduct a power calculation which will determine the sample size of a larger trial will be available as a result of documented dropout rates and standard deviation of outcome measures.

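### Serious adverse events feed the progression decision, but the waitlist's no-contact wait makes its events liable to be under-recorded, and counting occurrence alone cannot separate background events from related ones

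*Protocol article*

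**What the plan says.** All references are to the Protocol article.

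- **Progression (Discussion).** The article says that "this research will determine if the intervention should progress to a full RCT". It names four inputs: acceptability, then "the occurrence of serious adverse events occur, the appropriateness of research measures and adherence rates which should be over 85" per cent. Only adherence has a threshold. Nothing is said about comparing events between arms or about relatedness.
- **Expected events (Adverse events).** The article warns that "the population we are studying has a natural disease progression, and severe events such as a death may occur", and adds that unforeseen risks are possible at this stage. The recording rule is that "any adverse events will be documented and the ethics committee notified". It is not limited to one arm.
- **Waitlist arm (Waitlist group).** "The waitlist control group will not receive any interaction with the research team during the 6-month wait period". These participants "will complete baseline measures at the start and the end of the waitlist period". "Once the wait period is completed, they will take part in the intervention", with measures at its end and 2 weeks later.
- **Intervention arm (Intervention group; Table 2).** Four weekly sessions, a contact 2 days before each, and measures at the end of the intervention (taken in the fourth session), at 2 weeks and at 6 months after it.
- **Instruments (Quantitative outcome measures).** SAQOL, SSES, NEADLS and HADS, covering quality of life, self-efficacy, daily activities and mood.

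**The concern.** The study has a randomised control arm that could show how many serious events this population has without the intervention. The no-contact rule limits what that arm can show during the months when it would be informative. The progression sentence then looks at whether serious events occur, with no reference to the control arm or to cause.

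Two things are at stake. First, if events come to light more readily in the intervention arm, a comparison of recorded counts leans against the intervention even when it is harmless. Second, in a population where such events are expected anyway, their mere occurrence says little about whether the intervention is safe to take into a larger trial.

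**Working it through.** **Contacts after randomisation, from the article's own schedule**

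| | Intervention arm | Waitlist arm, up to the end of the wait |
|---|---|---|
| Pre-session contacts | 4 | 0 |
| Sessions | 4 | 0 |
| Measures outside sessions | 2 (2 weeks and 6 months after the intervention) | 1 (end of wait) |
| Total | 4 + 4 + 2 = 10 | 1 |
| Time of last measure | 4 weeks + 6 months, about 7 months | about 6 months |

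The end-of-intervention measure is taken in session four, so it is not counted twice. Nine of the ten intervention-arm contacts fall within 4 + 2 = 6 weeks of the first session or just before it. That arm then has its own gap of about 5½ months (6 months less 2 weeks). The weekly phase is 4 of about 26 weeks, or 15%.

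Two features follow. The arms differ in the number of occasions on which an event could be noticed, and their observation windows differ by about a month. In addition, none of the four instruments is described as recording deaths, admissions or new strokes, so completing them at 6 months does not by itself bring events out. A participant who has died or is too ill may appear only among the non-returns that the Questions 1–4 analysis counts.

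**Illustration of unequal capture**

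The article states no event rate or capture rate, so there is no figure of its own to reproduce here beyond the sample size: 50 + 10 = 60 (Sample size). The Randomisation section says that blocking gives balanced numbers, from which n = 30 per arm is inferred.

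Assumptions: the same true six-month risk r in both arms (5%, 10% or 20%), at most one event per person, and a fraction f of events recorded.

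- Recorded events in an arm: X ~ Binomial(30, r·f), with expected number 30·r·f.
- Chance that the intervention arm records more: P(X_I > X_W) = Σᵢ Σ_{j<i} P(X_I = i)·P(X_W = j).

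With full capture in the intervention arm, the expected recorded events there are 30 × 0.05 = 1.5, 30 × 0.10 = 3.0 and 30 × 0.20 = 6.0.

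| Waitlist capture | Expected waitlist events (r = 5%, 10%, 20%) | P(intervention arm records more) |
|---|---|---|
| 100% | 1.5, 3.0, 6.0 | 38%, 41%, 44% |
| 80% | 1.2, 2.4, 4.8 | 44%, 52%, 59% |
| 50% | 0.75, 1.5, 3.0 | 56%, 69%, 82% |

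Full capture in the intervention arm is generous, given that arm's own gap. With 80% capture there and 50% in the waitlist, the chances are 47%, 58% and 69%, against 36%, 40% and 43% when both arms capture 80%. The tilt is smaller but in the same direction.

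**Occurrence as a criterion**

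The chance of at least one background event among 30 people is 1 − (1 − r)³⁰, which is 79%, 96% and over 99% at r = 5%, 10% and 20%. This does not measure unequal capture, since it is the same for either arm. It shows only that, at these assumed rates, some event is likely in the intervention arm even if the intervention is harmless.

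**The case against.** A reader might infer that background events would appear only in the intervention arm. The article does not support that. The waitlist is measured at the end of the wait and then enters the intervention, so events can surface, and the duty to document covers any adverse event in either arm.

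A reader might also infer that the intervention arm is seen weekly throughout, or that serious events decide progression. Weekly contact lasts 4 weeks, and both arms are without scheduled contact for most of the period. Serious events are one of four inputs, with no threshold and no stated stopping rule.

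Three further objections deserve weight. A waitlist without research contact is a legitimate control condition in a study described as minimal risk. Single events can be judged for relatedness without a control rate, and the management panel includes medical input. And a journal article may leave the way events are elicited to the full protocol, which is not shown.

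These arguments limit the point but do not remove it. The point does not rest on a missing procedure. It rests on two things the article does state: a rule of no contact during the wait, and a progression input worded as occurrence. Followed as written, they give unequal opportunity to record events and a criterion that uses neither the control arm nor relatedness. A duty to document does not by itself produce detection where there is no contact.

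**Conclusion.** The point holds as a cheap improvement to a workable design. Serious events during the wait are liable to be under-recorded relative to the intervention arm, and "the occurrence of serious adverse events occur" does not, as a criterion, distinguish background from intervention-related events.

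The size cannot be fixed from the article. Under an assumed equal risk of 5% to 20%, about 30 per arm and full capture in the intervention arm, the chance that this arm records more events moves from about 38–44% at equal capture to about 56–82% if half of the waitlist events are captured. If waitlist capture at the end of the wait is good, the tilt is modest: 44–59% at 80% capture. The claim that the safety input is certain to be biased against the intervention would go too far, because the article gives no rule for how events count.

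**What to change.** 1. Add the same short, dated items on serious events (death, hospital admission, new stroke) to the waitlist's existing end-of-wait questionnaire and to the intervention arm's 6-month questionnaire. Check non-returns in both arms for death or admission.
2. Count events over the same 6 months from randomisation in both arms. Dating the events allows this although the intervention arm's last measure falls at about 7 months. Tabulate by randomised arm with person-time.
3. Reword the progression sentence in the Discussion so that it considers serious events by arm together with events judged related to the intervention, rather than occurrence alone.

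The cost is a few items on questionnaires already collected, a check on non-returns, and one sentence. The no-contact wait is kept. The drawbacks are recall over about 6 months (slightly longer in the intervention arm) and a background rate that stays imprecise with about 30 per arm, so the table should be read as description and not as a test.
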